**Methods:**

The present study is an active COVID-19 vaccine safety surveillance through an observational prospective cohort study that will be conducted in vaccination centers in Iran. The study will be conducted in twelve provinces of Iran. Study sites are vaccination centers where the AstraZeneca vaccine is administered to the cohort population. The study population includes all individuals who have received two doses of Sinopharm or Sputnik V vaccines and either the first or second booster dose of AstraZeneca according to the national guidelines for immunization in Iran in 2023. We are planning to include 30,000 eligible people in this study. Each individual will be followed up for 13 weeks after either the first or second booster dose of the AstraZeneca vaccine. Furthermore, convenience sampling is used to include participants in the present study. Participation in the study will be strictly voluntary.

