### Subject recruitment and follow up

People who approach to one of the vaccination centers for booster vaccination, if they are eligible to be included, they will be consulted and get informed about the project. If they accept to participate, they will be asked to sign the consent form. On a day of vaccination, all the required information will be recorded on a web-based questionnaire. For weekly follow up, the study staff will call the participant by phone to collect data if the participant do not use the web application for self-reporting of adverse event. After two unsuccessful attempts to contact the participant by telephone, their next of kin will be contacted. After two unsuccessful attempts to contact their next of kin, the participant will be considered lost to follow-up if they do not complete the questionnaire by self-report. In fact, the participants are able to provide self-reported answers to all web-based questions using the mobile phone or a computer. The attempts to contact will be documented. We will record the underlying reason for withdrawal. Withdrawn participants and those lost to follow-up will not be replaced after the enrolment period has ended.

To identify SAEs and AESIs, each individual will be followed-up for 13 weeks after the booster dose of the AstraZeneca vaccine. The diagnoses reported by the participants during follow-up will be examined by a scientific committee including specialists in the field of infectious diseases, epidemiology, virology/immunology, internal diseases and others if needed. Such committees have been established by each university and they are involving in confirming the diagnosis for all SAEs and AESIs. In addition, there is a national committee to investigate adverse events related to vaccines, and therefore for all SAEs and AESIs, the patients’ files will be discussed in such committee. Such investigation helps participants to be treated within a standard protocol under the supervision of a scientific group.

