### Interim analyses and reporting

For the study outcomes, interim analyses will be performed monthly but the formal report will be released within 1.5, 3, and 6 months. Such reports will be disseminated to all formal organizations and Iranian medical universities (including the Iranian Ministry of Health and Medical Education and WHO by request). In addition, the report will be published in relevant medical journals.

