### Statistical analysis

In the present study, the data on SAEs and AESIs will be included for the whole cohort population. People who do not report any event(s) will be considered as participants without event(s). As AESIs can occur even after 42 days following the first booster dose, the sensitivity analysis will be done excluding those AESIs occurring within the first 12 days after the second booster dose.

We will calculate the frequency and proportion of participants reporting AESIs and SAEs by time since vaccination. For the proportions, 95% confidence intervals will be calculated using an exact method.Observed-to-expected analyses will be conducted for SAEs and AESIs with an unknown risk window (most likely situation). The observed incidences for AESIs will be compared with background rates from the most appropriate sources. The expected rate will be age-stratified, and the standardized incidence ratio (SIR) will be calculated.Incidence rate of severe COVID-19 disease (any COVID-19 disease diagnosed by a healthcare professional, laboratory-confirmed COVID-19, hospitalization for COVID-19, COVID-19 requiring intensive care unit (ICU) admission, COVID-19 disease resulting in death) will be calculated after either the first or the second booster dose of the AstraZeneca and within the period of follow-up.

The present study will be performed in line with the international ethical guidelines for epidemiology studies published by the Council for International Organizations of Medical Sciences (CIOMS), the Declaration of Helsinki and its amendments, good epidemiological practice (GEP) guidelines and the Iran National Committee for Ethics in Biomedical Research. Data protection and privacy regulations will be strictly observed in capturing, forwarding, processing, and storing individuals’ data. The study protocol and informed consent forms will be reviewed and approved by the Iran National Committee for Ethics in Biomedical Research.

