The present study can provide a first estimate of the incidence of SEAs and AESI and will give first insights into the incidence of new cases of Covid-19 among the cohort population after heterologous booster vaccination with AstraZeneca vaccine. In addition, it will help to measure the break through infection after booster vaccination.

There are some challenges in the present study. In the last years, the response rates tend to be low in population-based studies considerably [31, 32]. A low response rate might affect the representativeness of the cohort population which might have an effect on the generalizability of the incidence of SEAs and AESI in the Iranian source population.

Regarding that each individual should be followed-up for 13 weeks after either the first or second booster dose of the AstraZeneca vaccine, some participants might be lost to follow up due to a serious outcome such as severe events, hospitalization, or death. Some participants might not tend to be followed up for such a long time of 13 weeks. Also, some individuals may fail to complete the electronic questionnaire weekly because of poor access to a smartphone or forgetfulness. For participants who do not complete the electronic questionnaire regularly, the cohort vaccinators will contact them and fill out the follow-up questionnaire.

One of the major concerns is related to the new coming information regarding the safety of the AstraZeneca and the side effects which might lead to the AstraZeneca refusal among the cohort population [33]. This may in turn decrease our chance to reach the predefined sample size of our study.

Currently, we face remarkable low coverage of third or/and fourth doses of COVID-19 vaccine among the general population in Iran. To date (June 21, 2022), 27,685,680 people have received the third dose of the COVID-19 vaccine, while the amount for the second dose is 57,959,218. Given the notable decreasing trend of the first and second booster doses of vaccination, we might achieve the study sample size (30,000 people) within a longer period of time.

In addition, we will not monitor reactogenicity for either the first or the second booster dose of the AstraZeneca vaccine. In the present study, we just aim to investigate the SAEs (hospitalization, death), AESIs that result in hospitalization, and severe COVID-19 disease.

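### Anyone who reports nothing is counted as event-free in the whole cohort, with no exception for lost or withdrawn participants, so SAE and AESI proportions are biased downward

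*Protocol article*

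**What the plan says.** In the protocol article, Statistical analysis, the denominator is set first: "the data on SAEs and AESIs will be included for the whole cohort population". The next sentence fixes how silence is coded: "People who do not report any event(s) will be considered as participants without event(s". The estimator is a proportion with an exact 95% interval: "We will calculate the frequency and proportion of participants reporting AESIs and SAEs by time since vaccination". For the comparison with background, "The expected rate will be age-stratified, and the standardized incidence ratio (SIR) will be calculated"; the person-time behind the expected count is not given.

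Other sections bear on this:
- Subject recruitment and follow up makes loss a status of its own. After two failed calls to the participant and two to the next of kin, "the participant will be considered lost to follow-up if they do not complete the questionnaire by self-report". Contact attempts and reasons for withdrawal are recorded.
- The Discussion concedes that "some participants might be lost to follow up due to a serious outcome such as severe events, hospitalization, or death".
- The Methods part of the abstract sets the observation window: "Each individual will be followed up for 13 weeks after either the first or second booster dose of the AstraZeneca vaccine".
- Interim analyses and reporting plans looks during follow-up: "interim analyses will be performed monthly but the formal report will be released within 1.5, 3, and 6 months".

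**The concern.** The rule treats absence of information as information. A participant who reported no event and then could not be reached, directly or through next of kin, stays in the denominator as a person without an event for the full 13 weeks. The Serious adverse events section defines an SAE as overnight hospitalization or death, and the Discussion names hospitalization and death as possible reasons for loss. The plan thus expects some of its outcome events to produce silence, and it codes silence as no outcome.

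In a safety cohort this error runs in the reassuring direction. It affects the first two specific objectives (SAE and AESI incidence within 13 weeks), and the results are meant for regulators and the immunization programme. This is a stated rule rather than a detail left to an analysis plan: a plan that censored lost participants would contradict the published sentence.

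**Working it through.** **1. The plan's own figure.** Sample size estimation gives 10,000 per vaccine to rule out an event with frequency 1 per 3,333.
- Rule of three: 3 × 3,333 = 9,999.
- Exact zero-event bound, one-sided 95%: ln(0.05) / ln(1 − 1/3,333) = 9,983.3, so 9,984.

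The figure reproduces, on the premise that all 10,000 are fully observed.

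**2. Bias in the proportion.** The documents give no loss rate, so these inputs are assumptions:
- d: share of participants lost;
- f: fraction of their 13 weeks seen before loss;
- RR: event rate in their unseen time relative to the rate in observed time.

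Events are taken as rare, and the rate in observed time is set to 1.
- Events seen: S = (1 − d) + d·f
- Events that occurred: T = S + d·(1 − f)·RR
- Reported / true under the plan's rule: S / T
- Reported / true with observed person-time as denominator: (S/S) / T = 1 / T

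For RR = 1, T = 1 and the plan's ratio is 1 − d(1 − f).

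| d | Rule, f=0, RR=1 | Rule, f=0.5, RR=1 | Rule, f=0.5, RR=2 | Rule, f=0.5, RR=5 |
|---|---|---|---|---|
| 10% | 0.90 | 0.95 | 0.905 | 0.792 |
| 20% | 0.80 | 0.90 | 0.818 | 0.643 |
| 30% | 0.70 | 0.85 | 0.739 | 0.531 |

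Example, d = 20%, f = 0.5, RR = 2: S = 0.8 + 0.1 = 0.9; T = 0.9 + 0.1 × 2 = 1.1; S/T = 0.818.

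S/T is below 1 whenever any event falls in unseen time, so the direction does not depend on why people are lost.

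**3. What person-time repairs.** With RR = 1 the ratio is 1.00 at every d and f. With d = 20% and f = 0.5 it is 1/1.1 = 0.909 at RR = 2 and 1/1.4 = 0.714 at RR = 5. Censoring removes the part unrelated to outcome and only some of the rest.

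**4. Interval width.** Zero events among 10,000 gives an upper bound of 1 in 3,339. If 10%, 20% or 30% are in fact unseen, the information is that of 9,000, 8,000 or 7,000 people. The bounds are then 1 in 3,005, 1 in 2,671 and 1 in 2,337, yet the rule would still print 1 in 3,339. The 10,000 planned for Sputnik V leaves no slack. The 20,000 planned for Sinopharm does: 14,000 would remain at 30% loss.

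**5. SIR.** If the expected count uses every enrolled person for 13 weeks, the SIR shrinks by the factor in step 2. With d = 20%, f = 0.5, RR = 1, a true 1.5 reads 1.5 × 0.90 = 1.35. If it uses observed person-time, that case is unbiased. At RR = 2 it reads 1.5 × 0.909 = 1.36, against 1.5 × 0.818 = 1.23 with whole-cohort time.

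**6. Interim reports.** Assume the reporting clock starts with the study and accrual is uniform for at least 26 weeks. Mean observed share of 13 weeks among those enrolled at week t:
- t = 6.5 (1.5 months): 6.5 / (2 × 13) = 0.25, and nobody has reached 13 weeks.
- t = 13 (3 months): 13 / (2 × 13) = 0.50.
- t = 26 (6 months): half complete, half averaging 0.5, so 0.75.

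**The case against.** **The sentence may mean only people who were contacted and reported nothing.** Loss is a separate recorded status, so this reading is possible. But the preceding sentence sets the whole cohort as the population and no exception follows. At best the text is ambiguous on a point that determines the estimate. Someone who reported an event before being lost does remain a case.

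**There are safeguards.** Missing web entries trigger staff calls and then next-of-kin calls. Deaths are reported by next of kin, and hospitalizations by participant or next of kin (Serious adverse events). Hospital documents and committee files are also outcome sources (Source documents). These are aimed at the loss the Discussion describes and will reduce the bias. They do not remove it: the committees examine diagnoses that participants report, and the rule operates where both participant and next of kin could not be reached.

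**Events are tabulated by time since vaccination.** That helps only if each period's denominator is the people still observed, which the whole-cohort wording does not provide.

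**Every SIR might be inferred to be biased.** The document does not support this, because the person-time behind the expected count is unstated. With observed person-time, loss unrelated to outcome does no harm to the SIR.

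**Incomplete follow-up might be inferred to distort the final results.** It does not. The study ends when the last participant enrolled reaches 3 months, so this part concerns interim reports only. The 25/50/75% figures also rest on an assumed clock and uniform accrual, while the Discussion describes falling booster uptake.

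**Conclusion.** The concern stands. Followed as written, the rule biases SAE and AESI proportions downward and makes their exact intervals too narrow. SIRs are biased too if the expected count uses whole-cohort 13-week time, and under outcome-related loss whichever person-time is used. Confidence is high for the direction. The size is not known, since no loss rate is given and the success of next-of-kin and hospital tracing cannot be judged from the document. The range to keep in mind is 0.70 to 0.95 of the truth for 10% to 30% loss unrelated to outcome, and lower if loss is outcome-related.

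A reader might infer a much larger effect. With 20% lost, triple risk and none of their events captured, the ratio is 0.8 / (0.8 + 0.2 × 3) = 0.57, and a true SIR of 1.5 would read 0.86 with whole-cohort time. This is an extreme assumed case: it needs loss from the first day and complete failure of the back-up sources. Nothing in the document supports it as the expected size. Even there, censoring alone would raise the ratio only to 1/1.4 = 0.71.

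**What to change.** Replace the sentence on non-reporters with wording to this effect:
- A participant counts as event-free only for time covered by a completed contact. Follow-up is censored at the last completed contact, day 91 (13 × 7) or the data cut, whichever comes first.
- SAEs and AESIs are reported as events per person-time and as a 13-week cumulative incidence that adjusts for censoring (Kaplan-Meier, or Aalen-Johansen with death as a competing event).
- Observed and expected counts in each SIR come from the same person-time, and the section says so.
- Because censoring does not cure outcome-related loss, a sensitivity analysis gives the unobserved time of lost participants 1, 2 and 3 times the observed event rate, over a range of loss.

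The same definitions should apply to the interim reports.

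The cost is a little more analysis work. Contacts are weekly and attempts are documented, so the dates should be available, and the call procedure need not change. Reported incidences will be higher and intervals wider, by amounts that depend on the loss that occurs.

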### Study period

The time point for enrolment will be either the first or second booster vaccination with AstraZeneca in one of the study sites, after primary vaccination with Sinopharm or Sputnik V.

Each individual will be followed-up for 13 weeks after either the first or second booster vaccination with AstraZeneca vaccine. Thirteen weeks follow-up period was chosen because this covers the most common risk windows for AESIs (42 days).

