### Sample size estimation

Regarding the WHO’s protocol, the sample size required to rule out an event with a frequency of 1 per 3,333 with a 95% confidence interval is 10,000 per vaccine [11]. Therefore, we are planning to include 20,000 and 10,000 eligible people with previous vaccination with Sinopharm and Sputnik V respectively. Regarding the higher proportion of immunization coverage for the Sinopharm vaccine compared to Sputnik V in Iran, we will include more vaccinated people with the Sinopharm vaccine in the present study. Participants will be considered to have completed the study when they have completed the last questionnaire 13 weeks after the booster dose. The end of the study is defined as the point at which the last subject enrolled has reached the 3 months follow-up period. In this study, convenience sampling will be used to include eligible participants until achieving the required sample size.

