### Study variables

Our independent variables include:

Age: Calculated as difference between enrolment date and the date of birth for people who will participate in the study.Gender (Nominal variable): Male/Female.Education (Ordinal variable): Total number of years of education.Self-reported underlying health condition (Binary variable: yes/no): An underlying health condition is a chronic or long-term illness, which in turn weakens the immune system.Self-reported weight (kg): The body weight for each respondent in our data set measured in kilogram.Self-reported height (cm): The body weight for each respondent in our data set measured in centimeter.Place of residence: The province where people live.Exact date of pervious vaccinations.

Other main variables of the present study gathered in enrollment and follow-up questionnaires is shown in Table 2.

**Table 2 Tab2:** The main variables of the study gathered in enrolment and follow up questionnaires

Participant information	AESI(Body system)	Follow-up questionnaire
Subject ID	Acute cardiovascular injury(Cardiac)	Hospitalization
Subject Name	Chilblain like lesions(Dermatologic)	Hospitalization date
Phone number	Single organ cutaneous vasculitis(Dermatologic)	Discharge date
Gender	Erythema multiforme(Dermatologic)	Hospitalization reason
Marital status	Pancreatitis(Endocrine)	Hospitalization diagnostics
Birth date	Subacute thyroiditis(Endocrine)	Hospitalization report
Educational attainment	Acute liver injury(Gastrointestinal)	Hospital ID
Income level	Coagulation disorder (thromboembolism)(Hematologic)	COVID-19COVID-19-Test
Place of residence	Thrombocytopenia(Hematologic)	COVID-19 Symptom Onset Date
Pregnancy status	Vaccine-associated enhanced disease (VAED)(Immunologic)	ICU admission
Breastfeeding status	Anosmia, ageusia(Gastrointestinal Respiratory)	ICU admission Date
Name of next kin	Anaphylaxis(Immunologic)	Death
Vaccine dose ID	Acute aseptic arthritis(Musculoskeletal)	Death date
Vaccination date	Rhabdomyolysis(Musculoskeletal)	Reason of death
Vaccine brand	Acute disseminated encephalomyelitis (ADEM)(Neurologic)	Pregnancy
Chronic respiratory disease	Bell’s palsy(Neurologic)	Abortion
Chronic heart disease	Generalized convulsion(Neurologic)	Menstrual irregularities
Chronic liver disease	Guillain-Barré syndrome (GBS)(Neurologic)	
Chronic renal disease	Meningoencephalitis(Neurologic)	
Diabetes	Acute renal injury(Renal)	
Immunocompromised / Immunosuppressed	Acute respiratory distress syndrome(Respiratory)	

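### The expected rate is stratified by age only although sex is recorded, so the SIR may be confounded by sex, chiefly for common outcomes such as hospitalization

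*Protocol article*

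**What the plan says.** The Statistical analysis section plans observed-to-expected analyses for SAEs and AESIs with an unknown risk window. On the reference it says: "The observed incidences for AESIs will be compared with background rates from the most appropriate sources". On the standardization it says: "The expected rate will be age-stratified, and the standardized incidence ratio (SIR) will be calculated". No stratifier other than age is named, and the sources are left open.

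The Study variables section lists "Gender (Nominal variable): Male/Female" among the independent variables, and gender also appears in Table 2 under participant information. It is given no stated role in the expected count.

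On how the cohort arises, the Sample size estimation section says that "convenience sampling will be used to include eligible participants until achieving the required sample size", and the Participants section makes participation voluntary. The Discussion concedes: "A low response rate might affect the representativeness of the cohort population". Sex is not mentioned there.

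Under Study outcomes, an SAE is an overnight hospital stay or a death. The section on recruitment and follow-up does not exclude pregnant women and counts maternal hospitalization among the maternal AESIs.

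**The concern.** The protocol describes no unvaccinated or concurrent comparison group, so the SIR is its only external comparison. How the expected count is built decides whether an SIR away from 1 can be read as a signal. With age strata alone, the expected count in each age band takes on the sex mix of the reference population. If the cohort's mix in that band differs, and the event is commoner in one sex, the SIR moves away from 1 with no vaccine effect. The direction can differ from one outcome to the next.

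Nothing in the sampling scheme secures the sex mix: no quota, no weighting and no stated check against the reference. For hospitalization the protocol itself suggests a sex difference. Overnight stays for pregnancy or delivery meet its SAE definition, can occur only in women, and fall within certain ages. Age strata cannot absorb that.

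At stake is either a false signal or false reassurance in results that are to go to the national regulators and the immunization program.

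**Working it through.** **The plan's own figure.** The sample size section says that "the sample size required to rule out an event with a frequency of 1 per 3,333 with a 95% confidence interval is 10,000 per vaccine". The rule of three gives 3 / (1/3,333) = 9,999, and the exact zero-event form gives ln(0.05) / ln(1 − 1/3,333) ≈ 9,984. The stated figure reproduces and does not depend on this point.

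**Inputs from the documents.** On cohort size: "we are planning to include 20,000 and 10,000 eligible people with previous vaccination with Sinopharm and Sputnik V respectively", 30,000 in all. On follow-up: "Each individual will be followed-up for 13 weeks after either the first or second booster vaccination with AstraZeneca vaccine". With no loss, person-time is 30,000 × 13/52 = 7,500 person-years.

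**Inputs that the documents do not give.** The sex mix of the cohort, the sex mix of the reference and background rates by sex are all assumed below. The reference is taken as 50:50, and the shares and rate ratios as equal across age bands.

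**Step 1: shift in the SIR when there is no true effect.** Let *m* be the share of the cohort in the sex with the higher rate, and *r* the ratio of the higher to the lower rate.

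Null SIR = [m·r + (1 − m)] / [0.5·r + 0.5]

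If the over-represented sex has the lower rate, the numerator becomes m + (1 − m)·r.

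| Cohort mix | r | Event commoner in the over-represented sex | Event commoner in the other sex |
|---|---|---|---|
| 50:50 | any | 1.00 | 1.00 |
| any | 1 | 1.00 | 1.00 |
| 60:40 | 2 | 1.60/1.5 = 1.07 | 1.40/1.5 = 0.93 |
| 65:35 | 2 | 1.65/1.5 = 1.10 | 1.35/1.5 = 0.90 |
| 80:20 | 2 | 1.80/1.5 = 1.20 | 1.20/1.5 = 0.80 |
| 80:20 | 3 | 2.60/2 = 1.30 | 1.40/2 = 0.70 |

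The last row is an extreme case. Computing expected counts by age and sex returns every entry to 1.00.

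**Step 2: random error for rare AESIs.** The background rates here are assumed, and the limits are exact Poisson.

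- At 10 per 100,000 person-years, 0.75 events are expected. With 1 observed, the 95% limits of the SIR are about 0.03 to 7.4.
- At 100 per 100,000, 7.5 are expected. With 7 observed, the limits are about 0.38 to 1.92.

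A shift of 10%, or even 30%, lies well inside these limits.

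**Step 3: random error for a common outcome.** Assume 5 hospitalizations per 100 person-years, so 0.05 × 7,500 = 375 expected. With 375 observed, the limits are about 0.90 to 1.11. With no true effect:

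- a factor of 1.10 puts the lower limit above 1 in about 48% of studies, against a nominal 2.5%;
- a factor of 0.90 puts the upper limit below 1 in about 50%;
- for assumed rates of 2 to 10 per 100 person-years (150 to 750 expected), the figure for a factor of 1.10 runs from about 23% to 76%.

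**The case against.** The strongest reply is that the bias is not shown. It needs both a within-age sex mix that differs from the reference and a background rate that differs by sex. The documents give neither the mixes nor the rates. That stands: a reader might infer that the SIR *is* confounded, but the text supports only that it may be.

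A reader might also infer from the Background that the need for a recognized travel certificate drives demand for this brand and skews who enrols. That section says only that some countries admit travelers given certain vaccines, AstraZeneca among them, and that people given unrecognized vaccines have trouble traveling. It does not link this to demand for AstraZeneca, and it says nothing about sex. It is no evidence of a skewed sex mix.

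A third reply is that this is a condensed article. Naming age does not rule out further strata, and the background sources are still open. That is fair as far as it goes. But the sentence states a method with one stratifier rather than leaving the matter unsaid, so correcting the sentence is reasonable.

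A fourth is that the three specific objectives are incidence estimates, which sex standardization does not touch, and that random error swamps the shift for rare AESIs. Both parts stand. They narrow the point to the SIR, and within it to common outcomes. The observed-to-expected sentence does cover SAEs, although the next sentence, on background rates, names only AESIs.

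**Conclusion.** The point holds as a possible confounding of the SIR that the plan can cheaply prevent. It is not a demonstrated bias. Its size rests wholly on assumed values: a null SIR of 0.90 or 1.10 for a 65:35 cohort at a 2:1 rate ratio, and 0.80 to 1.20 for mixes up to 80:20 at the same ratio. It is exactly 1.00 if the sex mix matches or the rate does not differ by sex.

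In practice it matters chiefly for common outcomes such as overnight hospitalization. There an error of 10% is about as large as the half-width of the confidence interval at the assumed rate, and the protocol's own definitions let pregnancy-related stays in. For rare AESIs it would not change a conclusion. The sample size and the incidence estimates are unaffected.

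**What to change.** In the Statistical analysis section, replace the sentence on the expected rate with: *expected counts will be computed by age group and sex, applied to person-time in each cell*. Prefer background sources that report age-by-sex rates. Use age-only rates only where no sex-specific rate exists, and flag those SIRs in the report.

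The cost is small. Age and sex are already collected, and expected counts are summed over cells, so sparse cells in the cohort do no harm. The downside is that sex-specific rates may be unavailable for some AESIs. Because the sources are not yet fixed, how many cannot be told from the documents.

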#### Specific objectives

To Estimate the incidence of different types of serious adverse events (SAEs) within 13 weeks in all enrolled vaccinated individuals after either the first or second booster vaccination with AstraZeneca.To estimate the incidence of different types of adverse events of special Interests (AESIs) within 13 weeks.To estimate the incidence of COVID-19 after either the first or second booster dose of A in all enrolled people.

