#### Sever COVID-19

Severe COVID-19 disease is defined as COVID-19 disease resulting in blood oxygen saturation < 90%, signs of pneumonia and signs of severe respiratory distress. Occurrence of COVID-19 disease will be solicited throughout follow-up to collect information on laboratory-confirmed diagnosis or not [12]. In the present study, the occurrence of COVID-19 is based on clinical manifestations diagnosed by health professionals or/and the polymerase chain reaction (PCR) test.

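### The analysis section applies the label severe COVID-19 to a list that opens with any diagnosed case, contradicting the protocol's own definition of severe disease

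*Protocol article*

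**What the plan says.** The article describes the COVID-19 outcome in four places.

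- **Study outcomes, Sever COVID-19.** This paragraph first fixes what counts as severe: "Severe COVID-19 disease is defined as COVID-19 disease resulting in blood oxygen saturation < 90%, signs of pneumonia and signs of severe respiratory distress". It then handles occurrence separately: "the occurrence of COVID-19 is based on clinical manifestations diagnosed by health professionals or/and the polymerase chain reaction (PCR) test".
- **Statistical analysis.** The planned quantity is "Incidence rate of severe COVID-19 disease (any COVID-19 disease diagnosed by a healthcare professional, laboratory-confirmed COVID-19, hospitalization for COVID-19", and the parenthesis closes with intensive care and death.
- **Specific objectives.** The third objective has no severity limit: "To estimate the incidence of COVID-19 after either the first or second booster dose of A in all enrolled people".
- **Discussion.** Near its end the article says "we just aim to investigate the SAEs (hospitalization, death), AESIs that result in hospitalization, and severe COVID-19 disease". Earlier the same section promises first information on new COVID-19 cases and on breakthrough infection.

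Table 2 (Study variables) gives the main follow-up items. They include COVID-19 and its test, symptom onset date, hospitalization with reason, diagnostics and report, ICU admission, and death with its reason. Oxygen saturation and respiratory signs are not among them. Source documents adds hospital documentation and committee findings as outcome sources.

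**The concern.** An analyst given this text cannot comply with both the outcome definition and the analysis paragraph. The first two items under the severe label are, in substance, the protocol's own rule for counting any COVID-19. None of the five items is its clinical definition of severe disease.

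Severe COVID-19 is one of three named study outcomes. Results are to be analysed monthly, reported formally at 1.5, 3 and 6 months, and passed to regulators and the immunization program. Followed literally, the analysis would publish mild diagnosed or test-positive cases under the heading of severe disease after the booster. A reader could not set such a figure beside a severe-disease rate from elsewhere.

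**Working it through.** **1. The plan's own figure.** The only design figure is in Sample size estimation: "the sample size required to rule out an event with a frequency of 1 per 3,333 with a 95% confidence interval is 10,000 per vaccine". With zero events and a one-sided 95% bound, n = ln(0.05) / ln(1 − 1/3,333) = 9,984. The rule of three gives 3 × 3,333 = 9,999. Both reproduce 10,000, and neither uses any definition of COVID-19, so this point leaves the sample size untouched.

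**2. The definitions side by side.**

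| Item under the severe label in Statistical analysis | Place in Study outcomes |
|---|---|
| Any case diagnosed by a professional | Rule for occurrence of COVID-19 |
| Laboratory-confirmed case | Rule for occurrence (PCR) |
| Hospitalization for COVID-19 | Not in the severe definition |
| ICU admission for COVID-19 | Not in the severe definition |
| Death from COVID-19 | Not in the severe definition |
| (no item) | Severe definition: "blood oxygen saturation < 90%, signs of pneumonia and signs of severe respiratory distress" |

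The clinical definition has no counterpart in the analysis, and the first two analysis items belong to a different outcome.

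**3. Pooled reading.** Suppose the five items form one endpoint. The first item already contains nearly all the others, so the rate is close to that of any COVID-19. Let s be the share of diagnosed cases that are severe. Then

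overstatement = (rate of any COVID-19) / (rate of severe COVID-19) = 1/s.

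The documents give no s. As an assumption:

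| s | 50% | 33% | 20% | 10% | 5% | 1% |
|---|---|---|---|---|---|---|
| 1/s | 2 | 3 | 5 | 10 | 20 | 100 |

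The background section's national totals do not supply s. Deaths over cases is 143,093 / 7,488,493 = 1.9%, but that is a crude fatality ratio for the whole population and the whole pandemic, not a severity share in boosted adults.

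**4. Illustration in planned numbers.** Inputs from the documents: N = 20,000 + 10,000 = 30,000, and "Each individual will be followed-up for 13 weeks after either the first or second booster vaccination with AstraZeneca vaccine". Assumptions: 3% of participants have any diagnosed COVID-19 in 13 weeks, with no loss to follow-up.

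- Person-years (approximate): 30,000 × 13/52 = 7,500.
- Any COVID-19: 30,000 × 0.03 = 900 cases; 900 / 7,500 = 120 per 1,000 person-years.
- Severe at s = 50%: 450 cases; 60 per 1,000.
- Severe at s = 20%: 180 cases; 24 per 1,000.
- Severe at s = 5%: 45 cases; 6 per 1,000.
- Severe at s = 1%: 9 cases; 1.2 per 1,000.

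The pooled rule would report 120 per 1,000 as severe in each of these cases. The assumed 3% scales the counts and rates but cancels from the ratio.

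**5. Tiered reading.** Suppose each of the five items gets its own rate. The hospitalization, ICU and death rates are then what they claim to be, and the first two answer the third objective. Nothing need be inflated. Two defects remain: the first two tiers sit under a severe label, and the saturation-based definition is still not estimated.

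**The case against.** The strongest reply is that the parenthesis is a list of tiers. As a pooled endpoint its later items would be almost redundant, so separate rates are the more natural reading. This stands as far as magnitude goes: a reader might infer that the plan inflates severe incidence many-fold, but that needs both the pooled reading and a value of s that the protocol does not give. The reply does not save the wording. The text announces a single incidence rate, puts severe over every tier, and omits the definition it gave earlier.

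Two further replies are sound.

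- A reader might take the Discussion to confine the study to severe COVID-19. The closing sentence does say so, but it follows a remark that reactogenicity will not be monitored, and the same section promises incidence of new cases and breakthrough infection. The Discussion is mixed and cannot decide the question.
- A reader might conclude that the saturation, pneumonia and distress criteria cannot be scored at all. Table 2 lists only main variables and includes hospital diagnostics and reports; Source documents names hospital documentation. Those records could supply the criteria for admitted cases, and item-level detail may sit in the full protocol. What can be said is that no listed variable records them directly.

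It is also fair that the study's main purpose is vaccine safety, and that observed-to-expected comparisons are planned only for SAEs and AESIs.

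**Conclusion.** The contradiction is established from the text and rests on no assumption: Statistical analysis calls severe what Study outcomes treats as occurrence of any COVID-19, and it never analyses the stated severe definition. The objectives and the Discussion do not resolve which outcome is meant.

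The numerical consequence is conditional. Under pooling, any COVID-19 contains severe COVID-19, so the rate is overstated whenever some diagnosed cases are not severe; the factor is 1/s, from 2 to 100 for an assumed s of 50% down to 1%. Under separate tiers the effect is mislabelling of two tiers, with no rate necessarily too high. Either reading calls for the same correction. The harm is confined to the COVID-19 outcome.

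**What to change.** Reconcile Specific objectives, Sever COVID-19, Statistical analysis and the Discussion by naming two outcomes, each with its own incidence rate.

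1. **Any COVID-19:** professional diagnosis and/or PCR, with laboratory-confirmed cases also shown separately. This answers the third objective.
2. **Severe COVID-19:** one definition used throughout. Either (i) hospitalization, ICU admission or death for COVID-19, or (ii) the existing saturation, pneumonia and respiratory-distress criteria, taken from hospital documentation, with the source stated.

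Remove the diagnosed-case and laboratory-confirmed items from the severe label.

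**Cost.** Option (i) is a wording change, since Table 2 already holds the events and the reasons for hospitalization and death. It would replace the present clinical definition, and its overnight admissions and deaths will also count as SAEs, which the report should say. Option (ii) keeps the definition but needs extraction from hospital records and would miss severe cases that were never admitted.

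Under both options the severe rate becomes smaller and its interval relatively wider. In the illustration above, the approximate relative half-width (1.96/√cases) goes from 1.96/√900 = 6.5% for any COVID-19 to 1.96/√45 = 29% for severe disease at s = 5%. The SAE and AESI analyses and the sample size do not change.
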